## Abstract

**Introduction::**

There is a lack of published studies about the combination of duloxetine and pelvic floor muscle training (PFMT) in women with stress urinary incontinence (SUI). The aim of our work will be to evaluate the effect of this intervention by assessing whether there is a change in the incontinence episode frequency (IEF), Incontinence Quality of Life (I-QoL), Patient Global Impression of Improvement score (PGI-I) and mean time between voids (MTBV). Combined therapy with duloxetine and PFMT will be compared to duloxetine treatment alone with respect to its efficacy and side effects.

**Methods::**

This study will be a randomized intervention, parallel, multicenter study in collaboration with 45 urological outpatient clinics at the national level. Patients will be assigned in a 1:1 ratio to the experimental and control groups using simple randomization according to odd and even numbers assigned sequentially to the patients at each clinic. The experimental intervention will be 12 weeks. The experimental group will receive oral treatment with duloxetine at a daily dose of 2 × 40 mg and will be required to perform innovative PFMT. The control group will receive the same oral duloxetine treatment (2 × 40 mg a day) but will not perform PMFT. Data will be collected from both groups before intervention and after the 12-week intervention is completed.

**Discussion::**

The study protocol presents the starting points, design and randomization of an interventional multicenter study to monitor the effect of the combination of duloxetine with innovative PFMT compared to duloxetine treatment alone in women with SUI. This study may provide evidence of the efficacy of this combined treatment for SUI and highlight benefits associated with active approaches to treatment through exercise.

**Registration::**

This study was retrospectively registered in the ClinicalTrials.go NCT04140253. Protocol version 1.0. date 11.1.2019.

## Introduction

1

Urinary incontinence is an involuntary leakage of urine; the most common type is stress urinary incontinence (SUI). SUI is defined as “the complaint of involuntary loss of urine on effort or physical exertion (eg, sporting activities), or on sneezing or coughing”.^[1]^ According to an international consensus, the average prevalence of urinary incontinence is approximately 20% to 30%, and in half of these cases, it is classified as SUI. The estimated prevalence of urinary incontinence in 15-year-old women is 5%. It increases with age to 72% in 60-year-old women.^[2]^ The first-choice treatment to improve SUI is pelvic floor muscle training (PFMT). It is defined as repeated, selective-will contraction and relaxation of specific pelvic floor muscles. It is important to exercise the strength, endurance and relaxation of pelvic floor muscles.^[2,3]^ The PFMT mechanism of action is pelvic floor muscle hypertrophy, which decreases urethral hypermobility and thus reduces urinary incontinence.^[4,5]^

In the literature, there is a lack of published studies that examine a combination of duloxetine and PFMT in women with SUI. In order to ensure the maximum effect and safety of these interventions, it is necessary to continually innovate exercise programs and to update knowledge with relevant guidelines. It is crucial that PFMT is progressive, that is, displays a gradual increase in difficulty. It is also important to ensure that the training program is interesting to keep patients motivated to complete it. In recent years, studies described PFMT using stabilization, so we decided to verify the effect of progressive PFMT with stabilizing exercises in combination with duloxetine.^[6]^

SUI treatment involves increasing the urethral closure pressure by correcting hypermobility, lengthening and strengthening urethral support or enhancing the intrinsic urethral closure mechanism. The hypothesis that elevated serotonin and noradrenaline levels in Onuf's nucleus stimulate the urethral sphincter has been confirmed experimentally.^[7,8]^ Duloxetine is a noradrenaline and serotonin reuptake inhibitor; it increases the synaptic concentrations of both mediators at Onuf's nucleus. Conversely, it minimally affects postsynaptic dopaminergic receptors.^[7]^ Duloxetine causes pudendal nerve stimulation and improves the tone of the sphincter urethra, effects that significantly increases urethral pressure in women with SUI.^[9]^

An initial phase II clinical trial evaluated the efficacy of duloxetine in 48 US centers. Patients aged 18 to 65 years with SUI were included in the trial. Treatment lasted 12 weeks after the screening and dose escalation phases. The efficacy of treatment was assessed by examining the incontinence episode frequency (IEF) each week, the Incontinence Quality of Life questionnaire (I-QoL), the Patient Global Impression of Improvement (PGI-I) and the mean time between voids (MTBV).^[10]^

Duloxetine significantly reduced the number of IEFs per week while improving quality of life according to I-QOL. It also increased the number of patients with positive PGI-I and increased MTBV. The changes were positively dependent on the duloxetine dose. Treatment discontinuation occurred in 5% of patients in the placebo group, 9% of patients taking 20 mg/day duloxetine, 12% of patients taking 40 mg/day duloxetine and 15% of patients taking 80 mg/day duloxetine. The most frequent adverse event was nausea, which occurred in 13% of the patients taking 80 mg/day duloxetine and was the reason for treatment discontinuation in 4.3% of cases.^[10]^

The majority of patients who received 80 mg/day duloxetine who reported nausea continued their treatment. Other undesirable effects included headache, dizziness, dry mouth, insomnia, constipation and nasopharyngitis. These side effects are rare and do not usually cause discontinuation of treatment. Because the 80 mg/day duloxetine dose most efficaciously improved urine leakage while not increasing the number of adverse events, it was recommended for use in a phase III clinical trial.^[10]^

The phase III clinical trial evaluated the clinical efficacy and safety of duloxetine at a daily dose of 80 mg (40 mg twice daily). The clinical trial was double-blinded and placebo-controlled. The clinical file, utilized methods and statistical analysis was similar to those used the phase II clinical trial. The mean percentage change in IEF and mean change in total I-QOL were similarly evaluated. Complete dryness was achieved in 10.5% of duloxetine-treated patients, while only 5.9% of participants in the placebo group achieved dryness. The number of patients who experienced decreased weekly urinary leakage rates (more than half) was significantly higher in the duloxetine group (51%) compared to the placebo group (34%). Nausea was the most common adverse side effect; it occurred in 23% to 28% of the patients taking duloxetine compared to 2% to 7% of participants in placebo group. Although this adverse event occurred in a quarter of all women taking duloxetine, it only caused premature treatment discontinuation in 3% to 6% of cases (it caused premature discontinuation of treatment in 1% of the placebo group). Most women reported nausea when treatment started and throughout the treatment period. Effects only reached a mild or moderate degree (75%–87% of all women with nausea). The nausea was transient in nature and subsided in 40% to 60% of cases after one week and 74% to 86% after 1 month of treatment passed. Thus, after a month of treatment with duloxetine, nausea was only reported in 3% to 7% of all treated women.^[8,11,12]^

Ghoniem et al demonstrated the effect of a 12-week combination of PMFT and duloxetine treatment on women with SUI. The number of IEFs per week, number of pads used, quality of life and subjective evaluation through the PGI-I scale were evaluated. The IEF responder rate in duloxetine vs PFMT group was 56.5% vs 26.1%, median decrease in pads used was 35.3% vs 24.8% and mean increase in I-QoL score was 8.3% vs 7.8%.^[13]^

Maund et al monitored both the benefits and adverse effects associated with duloxetine use for SUI treatment using a meta-analysis. Improvements were reported for reducing SUI symptoms and improving quality of life.^[14]^

### Primary goal

1.1

The primary goal of this trial is to assess the efficacy of combined duloxetine as comparator and innovative PFMT compared to duloxetine treatment alone in treatment of women with SUI. The primary goal will be monitored based on change in IEFs, according to the International Consultation on Incontinence Questionnaire Short Form (ICIQ-IU SF), over 12 weeks of treatment.

## Methods

2

### Study design

2.1

The Duloxing trial is designed as a randomized controlled intervention and parallel study. The Duloxing study will compare the effect of duloxetine as comparative registered treatment and duloxetine as comparative registered treatment plus innovative PFMT combination therapy within a female population with SUI. Study will examine the effect of authorized registered Duloxetine treatment in the population. The hypothesis states that after 12 weeks of combined treatment, the duloxetine plus PFMT group will have significantly fewer episodes of urine leakage, fewer collection aids and improvements reflected in quality of life assessments compared to the duloxetine alone group. This protocol was approved by the ethics committee of the University Hospital in Martin, Slovakia (number 24012019). All important protocol modifications will be approved by the same ethics committee. Informed consent will be obtain from trial participants by the local clinic of urology. The personal information about potential and enrolled participants will be collected, shared, and protected in concordance with Slovakian low.

### Recruitment and consent

2.2

The Duloxing study will be performed in 45 community clinics of urology in the Slovakia. The study will use 2 groups in parallel: the experimental group (E) and control group (C). The study will be randomized and controlled in a 1:1 allocation ratio. For the allocation process, sequences will be generated by a computer and designated by a researcher who will not participate further in the study. In this system, the computer generates even and odd patient numbers. Patients with odd numbers will receive duloxetine monotherapy at a daily dose of 2 × 40 mg per tablet for 12 weeks. Patients with even numbers will receive a combined treatment of duloxetine at a daily dose of 2 × 40 mg per tablet for 12 weeks combined with PFMT for the same time period. The generated numbers will be placed in sealed envelopes. Each envelope will contain the group code (E or C). Blinding will prevent intentional selection bias (Table 1).

**Table 1 T1:**
[figure not shown]
Recruitment, intervention and evaluation plan for experimental and control groups in the Duloxing study.

### Sample size

2.3

We used power analysis to determine an appropriate sample size; the test strength was set at 0.80 and alpha at 0.05 (type I error). An estimated 63 probands are required for each group (experimental and control). We anticipate a 20% loss in participation and will therefore include a total of at least 158 probands. Based on sample selection, we expect a decrease in incidence after intervention from 10% to 35%. A decrease of more than 50% will be considered a success.

Listed below are the inclusion and exclusion criteria for the DULOXING trial.

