## Discussion

3

The study protocol presents the starting points and design of a randomized-intervention, multicenter study with the aim of evaluating the effect of the combination duloxetine and PFMT therapy versus duloxetine treatment alone in women with SUI. The study may provide evidence of the efficacy of combined treatment for SUI and indicate an active approach for the treatment of SUI through exercise.

The strength of the study is it promotes an innovative, non-invasive and conservative treatment of strengthening pelvic floor muscles with stabilization exercises in addition to duloxetine treatment. We will use 3 standardized measuring tools: ICIQ-UI SF, OAB-q-short version and I-QoL. Both groups will receive daily oral 80 mg duloxetine (2 × 40 mg), and an innovative PFMT will be added in the experimental group. Interventions will last for 12 weeks, and will consist of exercise 5 times a week for 30 minutes. Education of probands regarding anatomy, physiology, and pelvic floor muscles—so that they properly understand the impact of exercises—will be done by a physiotherapist in collaboration with a nurse 5 times. Subsequently, exercises will be performed at home, and a diary control will be used to ensure compliance.

Based on similar studies, we expect good patient adherence, a low level of patient dropout and agreement with the study protocol. Patients who will be assigned to a duloxetine-only group will be offered the opportunity to exercise after of the 12-week treatment. We expect a 20% subject dropout. The success of our treatment will be a decline of more than 50% in the difficulties associated with SUI symptoms.

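### The only effect statement in section 2.3 (a decrease from 10% to 35%) cannot support 63 per arm at 80% power and fits no endpoint or analysis in the protocol

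*Protocol article*

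**What the plan says.** Section 2.3 (Sample size) sets the error rates: "the test strength was set at 0.80 and alpha at 0.05 (type I error"). It then gives the result, "An estimated 63 probands are required for each group (experimental and control"), and the allowance for loss: "We anticipate a 20% loss in participation and will therefore include a total of at least 158 probands". The only effect figures follow: "we expect a decrease in incidence after intervention from 10% to 35" per cent. The next sentence sets a success bar: "A decrease of more than 50% will be considered a success". The Discussion repeats that bar: "The success of our treatment will be a decline of more than 50% in the difficulties associated with SUI symptoms".

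Elsewhere, section 1.1 bases the primary goal on change in incontinence episodes as captured by the ICIQ questionnaire. Section 2.7.1 lists the ICIQ-UI SF and OAB-q scores as primary measurements. Inclusion criterion 5 requires at least seven episodes a week. Section 2.9 plans a general linear model and mixed-design repeated-measures ANOVA with partial eta squared. Both arms receive duloxetine. On the response to duloxetine without training, the Introduction reports that the share of women whose weekly leakage fell by more than half "was significantly higher in the duloxetine group (51%) compared to the placebo group (34" per cent).

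**The concern.** A power statement needs an outcome, a between-arm effect and a test that together produce the stated n. Section 2.3 offers one effect sentence, and on neither natural reading does it do this.

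- **As two rates,** 10% to 35% is an increase, although the sentence calls it a decrease.
- **As a range of reduction,** 10 to 35% lies wholly below the success bar set in the next sentence.
- **As an outcome,** incidence does not fit a trial in which every participant is incontinent at entry, or an ANOVA of continuous data.

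The 50% rule has its own gap. It names no measure and no contrast between arms. About half of women on duloxetine alone met a similar criterion in the trial described in the Introduction, so a decline within the combined arm would say little about what training adds.

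At stake is whether a reader can tell what difference the trial was designed to detect, and on what basis success will be claimed.

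**Working it through.** **Inputs.** Power 0.80, alpha 0.05, 63 per arm, 20% loss, 158 in total, and the figures 10% and 35%, all from section 2.3. Allocation 1:1 from section 2.2. Responder rates on duloxetine of 51% and 56.5% from the Introduction. Sidedness is not stated; two-sided is assumed, so z = 1.960 and 0.842.

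**1. Allowance for loss.** 2 × 63 = 126, and 126 / 0.80 = 157.5, rounded up to 158. The plan's total reproduces.

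**2. 63 from 10% and 35%.** With pooled variance, n = [z_a √(2p̄(1−p̄)) + z_b √(p1(1−p1) + p2(1−p2))]² / (p2−p1)².

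- p̄ = 0.225, so √(2 × 0.225 × 0.775) = 0.5906.
- √(0.10 × 0.90 + 0.35 × 0.65) = √0.3175 = 0.5635.
- n = (1.960 × 0.5906 + 0.842 × 0.5635)² / 0.25² = 42.6, so **43 per arm**.
- Continuity correction: (n/4)[1 + √(1 + 4/(n × 0.25))]² = 50.3, so **51 per arm**.
- Other two-sided methods: 40 (unpooled), 41 (arcsine), about 49 to 50 (Fisher exact). One-sided versions give 32 to 42.
- Exchanging the two rates leaves these sizes unchanged.
- Power with 63 per arm: Φ[(0.25√63 − 1.960 × 0.5906)/0.5635] = Φ(1.467) = **92.9%**.

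No variant at 80% power gives 63.

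**3. 63 from a difference in means.** n = 2(1.960 + 0.842)² / d². With d = 0.5 this is 2 × 7.849 / 0.25 = 62.8, so **63**. By the t test, 63 per arm gives 79.5% power and 64 gives 80.1%. The document does not state d = 0.5; it is solved back from n.

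**4. Which score difference d would describe.** The abstract has data collected before and after treatment. With two time points, the group-by-time term of the mixed ANOVA is the two-sample t test on change scores. If d = 0.5 were instead the difference at the final visit, with equal SDs and no baseline difference, the standardised difference in change would be 0.5/√(2(1−r)), where r is the assumed correlation between baseline and final score:

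| r (assumed) | d on change | Power, 63 per arm |
|---|---|---|
| 0.3 | 0.42 | 65% |
| 0.5 | 0.50 | 80% |
| 0.7 | 0.65 | 95% |

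A restated d must therefore say that it refers to change scores.

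**5. The success bar.** A reduction of at most 35% is less than 50%. If the figures were transposed (35% down to 10%), the relative fall would be 25/35 = 71%, which clears the bar, but the required n is still 43 or 51.

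**6. The 50% rule as a between-arm responder comparison,** using the formula in step 2 with 63 per arm. The control rates are borrowed from the Introduction, which is an assumption.

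- Control 51%: 80% power at about 75% in the combined arm (74.9%). Power is 64% for +20 points, 40% for +15 and 20% for +10.
- Control 56.5%: 80% power at about 80% in the combined arm.

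**The case against.** The strongest reply is that the effect sentence comes after the n and the allowance for loss, and nothing labels it as the input to the power calculation. On that view the 43, 51 and 93% figures test a reading the sponsor may never have intended. 63 is an ordinary two-mean sample size that suits the planned ANOVA, incidence is loose wording for episode frequency, and an article may leave the effect size to a fuller document.

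Much of this stands. A reader might infer that 63 or 158 is wrong, or that the trial is underpowered. The documents do not support that: step 3 gives a plausible source for 63, and step 1 confirms 158.

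A reader might also infer that the plan expects to fail its own criterion. That goes too far, because an average fall of 10 to 35% can coexist with a per-patient rule of more than 50%, and the Introduction reports duloxetine results with just such a responder measure. Nor does the 50% sentence replace the main comparison: sections 1.1 and 2.1 frame the aim and hypothesis as combination against duloxetine alone, and section 2.9 tests differences between the groups. Finally, a null result would still be interpretable through the confidence interval for the between-arm difference.

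What the reply does not remove is the sentence itself. It is printed as the expected effect in the sample-size section, is wrong or unclear on each reading, and refers to something the trial does not measure. That is a misstatement, not an omission.

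**Conclusion.** The point holds as a fault in what section 2.3 states, not as proof of a wrong sample size. On the two-rates reading, 10% and 35% call for 43 per arm (51 with continuity correction) against the stated 63, whose power would be 93% instead of 80%. On the range reading, the expected effect sits below the success bar unless the bar is a per-patient rule, which is nowhere stated. The 50% rule also lacks a named measure and a between-arm comparison.

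These results assume a two-sided test. The responder figures also assume that the Introduction's control rates carry over to this trial. That 63 came from a standardised difference of 0.5 is an inference from the arithmetic.

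Severity: should-fix. The remedy is wording, and the between-arm test in section 2.9 is unaffected.

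**What to change.** 1. Delete the 10% to 35% sentence from section 2.3.
2. Tie 63 per arm to the analysis in section 2.9: the between-arm difference in change from baseline (the group-by-time term) in one named primary score, at two-sided alpha 0.05.
3. State the detectable effect as a standardised difference of 0.5 in change scores, with 79.5% power by t test. The sponsor should confirm this or replace it with the assumption actually used.
4. Keep 158 for 20% loss.
5. In section 2.3 and the Discussion, define the 50% rule as a per-patient responder criterion on one named measure. Say that any claim of success rests on the comparison between arms, not on the decline within the combined arm. Add that 63 per arm detects about 51% against 75%, or 56.5% against 80%, with control rates borrowed from the Introduction as an assumption.

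The cost is rewording in two places and no extra patients. The downside is a stated power slightly below 80%, and an open acknowledgement that only a large difference in responder rates is detectable.

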### Inclusion criteria

2.4

1.Woman's willing to provide written informed consent;2.Women over 18 years old who experience uncomplicated SUI;3.Score on the International Consultation on Urinary Incontinence Questionnaire ≥14 points;4.Symptoms of urinary incontinence for at least 3 consecutive months;5.Have at least seven urinary incontinence episodes per week;6.Degree of pelvic organ prolapse ≤ stage 2;7.Willingness to accept the randomization process and fully participate in tests.

### Exclusion criteria

2.5

1.Recent use of any pharmacologic agent to treat symptoms of urinary incontinence in the past 6 months;2.History of anti-incontinence surgery in the past 12 months;3.Use of onabotulinum toxin A for the treatment of urinary incontinence in the past 12 months;4.History of pelvic prolapse repair or urethral surgery in the past 12 months;5.History of PFMT in the past 12 months;6.History of interstitial cystitis or bladder-related pain;7.Chronic severe constipation;8.Clinically significant renal or hepatic impairment;9.Clinically significant heart impairment;10.Women who are pregnant, lactating or actively trying to become pregnant;11.Non-compliance with limitation of duloxetine treatment for mixed urinary incontinence;12.Positive urinary tract infection;13.Use of rehabilitation aids (pessary, urethral plugs, vaginal beads, et cetera);14.Use of antidepressant(s);15.Insufficient understanding of pelvic floor exercises and/or omitting exercises;16.Participation in any clinical study in the past 6 months.

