#### Experimental group

2.6.2

PFMT with stabilizing exercises (Table 2)

1.Oral administration of treatment with duloxetine at a daily dose of 2 × 40 mg for 12 weeks.2.PFMT with lumbopelvic stabilization will be performed.3.PFMT exercises will be performed 5 times a week for 20 to 30 minutes a day, after initial training with a physiotherapist.a.Educating probands about anatomy, physiology and pelvic floor muscle functions;b.Training pelvic floor muscles in different positions;c.Training pelvic floor muscles with lumbopelvic stabilization.

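### Exclusion item 15 asks every candidate to understand pelvic floor exercises that only one arm is taught, so it cannot be applied equally to both arms

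*Protocol article*

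**What the plan says.** Section 2.5 of the protocol article gives one list of exclusion criteria for the whole trial. The first half of item 15 is "Insufficient understanding of pelvic floor exercises"; the item reads in full "Insufficient understanding of pelvic floor exercises and/or omitting exercises". Item 5 of the same list excludes women with "History of PFMT in the past 12 months".

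Teaching is described under the experimental group only. Section 2.6.2 states that "PFMT exercises will be performed 5 times a week for 20 to 30 minutes a day, after initial training with a physiotherapist", and its first component is "Educating probands about anatomy, physiology and pelvic floor muscle functions". The Discussion adds that this education "will be done by a physiotherapist in collaboration with a nurse 5 times. Subsequently, exercises will be performed at home". The one exercise record that the article names stands in the same place: "exercises will be performed at home, and a diary control will be used to ensure compliance".

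The abstract says that the control group receives the same duloxetine "but will not perform PMFT". According to the Discussion, controls are offered exercise once the 12 weeks are over.

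**The concern.** An eligibility rule should be answerable in the same way for every woman, before anyone knows her arm. Item 15 asks about understanding, and omission, of exercises that are part of the treatment under test and that half of the women are not meant to do. Two different biases can follow, depending on when the item is applied.

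- **Before allocation:** candidates have to meet the exercises in some form so that their understanding can be judged. Those who become controls then know something of a home programme that the design withholds from them. Any control who exercises narrows the difference between the arms.
- **After allocation:** only women assigned to PFMT can show poor understanding or omit exercises. Removing them takes the less able or less adherent women out of one arm and leaves their counterparts in the other. The comparison is then no longer as randomised.

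The first bias works against the combination and the second works for it. A reader of the results could not tell which had operated.

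**Working it through.** **1. The sections side by side**

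| Question | Protocol article | Consequence |
|---|---|---|
| Who is subject to item 15? | Single exclusion list, 2.5 | All candidates, both arms |
| Can candidates already know the exercises? | Item 5 bars PFMT in the past 12 months only | Some may, from earlier training; many will not |
| Who is taught? | 2.6.2, experimental group | Controls are not meant to be taught |
| What do controls do? | No PFMT for 12 weeks (abstract); exercise offered afterwards (Discussion) | Controls have no exercises to understand or omit |
| When is item 15 judged? | Not stated | Both readings remain open |

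Applied before allocation, the item requires some presentation of the exercises to any woman who does not already know them. Applied afterwards, it can be failed in one arm only. Neither reading treats the arms alike.

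**2. The plan's own sample size**

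Inputs from section 2.3: power 0.80, alpha 0.05, 63 per group, 20% loss, total at least 158. The number of sides is not given; two-sided is assumed.

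- Dropout: 63 / (1 − 0.20) = 78.75, rounded up to 79 per group; 2 × 79 = 158. This reproduces the stated total.
- The 63: n = 2 × (1.96 + 0.8416)² / d² = 15.70 / d². With d = 0.5 this is 62.8, rounded up to 63. The value d = 0.5 is an assumption, since the article gives no standardised difference. Reading its 10% and 35% as two proportions to be compared gives 43 per group, not 63.

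**3. Sensitivity to control-arm exercise (illustrative)**

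If a share c of controls gains a fraction b of the PFMT effect, the difference becomes d = 0.5 × (1 − c × b). Power is approximately Φ(d × √(63/2) − 1.96), with √31.5 = 5.612.

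| c | b | d | Power at 63 per arm | n per arm for 80% power |
|---|---|---|---|---|
| 0 | – | 0.50 | Φ(0.846) = 0.80 | 63 |
| 10% | full | 0.45 | Φ(0.566) = 0.71 | 78 |
| 20% | full | 0.40 | Φ(0.285) = 0.61 | 99 |
| 30% | full | 0.35 | Φ(0.004) = 0.50 | 129 |
| 20% | half | 0.45 | Φ(0.566) = 0.71 | 78 |

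The documents give no value for c or b. Full benefit from a screening explanation alone is the upper end, because the experimental arm also receives repeated education and supervised initial training. The half-benefit row shows a milder case.

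**4. The post-allocation reading**

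No figure can be put on this one. It would depend on how many women were removed from the PFMT arm and how their outcomes differed, and the article gives neither. Only the direction is clear: it favours the combination if the removed women did worse than those who stayed.

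**The case against.** A reader might infer that controls must be taught the exercises at screening, and that the comparator is therefore contaminated. The documents do not support this. No section provides for teaching or testing before allocation. For screening, 2.6.1 names only the usual procedure for indicating duloxetine. Section 2.10 says that 45 team members will explain the examination and exercise, but not to whom or when. Understanding could be judged from a short description, or come from PFMT more than 12 months earlier, which item 5 allows. A short check is also far from the full experimental component. And women who accept randomisation would ordinarily hear that one arm exercises, whatever item 15 says.

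It is also fair that the item, read whole, suits conduct after allocation at least as well, because trial exercises cannot be omitted before they are assigned. On that reading controls are taught nothing. But the item then becomes the one-sided exclusion described above, which is no safer.

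Finally, it would be too strong to say that control-arm exercise would go unrecorded. Section 2.8 says that adherence is recorded and does not limit this to one arm, the table with the evaluation plan is not shown, and case report forms are commonly left to a fuller document. What can be said is that the only exercise record the article names is the compliance diary described with the home exercises.

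These points remove any claim that contamination is established. They do not show a way to apply item 15 equally in both arms.

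**Conclusion.** The concern holds as a badly fixed eligibility criterion. Item 15 stands in a list for all candidates, conflicts with a design that gives exercise content to one arm, and has no stated time of assessment. Before allocation it carries an unquantified risk of dilution; after allocation it is a one-sided exclusion.

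The power losses to 0.71, 0.61 or 0.50 rest on an assumed d of 0.5, a two-sided test, assumed shares of controls who exercise, and full benefit in those women. They show what dilution could cost at the upper end and are not evidence that it will occur. The conclusion does not depend on them; it rests on the wording of sections 2.5 and 2.6.2 and the abstract. The repair is cheap and works under either reading, so it should be made.

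**What to change.** 1. In section 2.5, replace item 15 with a criterion that can be judged identically in every woman before randomisation without exercise teaching, for example being able to follow instructions and complete the questionnaires.
2. State that exercise education is given only after allocation and only to the experimental arm during the 12 weeks.
3. State that poor understanding or omitted exercises after allocation are recorded as adherence data, and that all women are analysed as randomised.
4. At the existing 12-week visit, ask both arms how often they did pelvic floor exercises during the treatment period, and report the answers by arm.

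The cost is amendment wording and one question at a visit already planned. The downside is that a few women who grasp the exercises poorly will be randomised to PFMT. The question at week 12 will not prevent control-arm exercise, but it will help the reader judge whether a small difference could reflect it.
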